## Heart rate variability

R-R intervals are derived from beat-to-beat blood pressure pulse intervals using finger plethysmography (Finapres® Nova, Ohmeda, Louisville, Colorado, USA) in all measurement rounds. Finger plethysmography-derived peak-to-peak intervals are highly correlated with ECG R-R intervals, with similar variability. The upstroke is determined using the pressure signal with a resolution of 2 ms, and the interval between the two consecutive upstrokes is measured. In the frequency domain, the two primary components are low-frequency (LF; 0.04–0.15 Hz) and high-frequency (HF; 0.15–0.40 Hz) spectra. Heart Rate Variability measures provide information primarily on vagal modulation with the LF power spectrum reflecting both sympathetic and parasympathetic modulation and HF acting as a surrogate marker of parasympathetic modulation of the R-R intervals [47]. The LF/HF ratio is used as an indicator of sympathovagal dominance [48]. All data acquisition and post-acquisition analyses will be carried out in accordance with the Task Force of the European Society of Cardiology and North American Society of Pacing and Electrophysiology [49].

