## Advanced Hemodynamics

Individuals will be monitored non-invasively with a Finapres® Nova (Ohmeda, Louisville, Colorado, USA) (volume-clamp technique) in all measurement rounds. In supine humans, the finger arterial pressure signal can be modelled to a reconstructed pressure curve, using a general inverse anti-resonance model [43]. Subsequently, the device calculate left ventricular stroke volume (SV) and use this with HR to provide a calculated measure of CO. Based on reconstructed Q waveforms, the Windkessel model parameters (R, C and ZC) will then be assessed by the system [44]. Plethysmography sensors will be placed in the second and third finger of the right hand. An oscillometric cuff will then be attached to the same arm and the device calibration is completed. Heart rate signal (HR) will be computed from a I lead digitized electrocardiogram (ECG), included in the equipment. Individuals will be studied for 15 minutes.

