### **Arterial Stiffness**

#### **Aortic and Limb Arterial Stiffness**

Arterial stiffness as measured by pulse wave velocity (PWV) obtained by applanation tonometry will be measured in all measurement rounds. A single operator locates the carotid, femoral, radial and distal posterior tibial arteries on the right side of the body and mark the point for capturing the corresponding pressure curves with two specific pressure sensitive transducers. The distance between the carotid and femoral, radial and distal posterior tibial arteries is measured directly and entered into the Complior Analyse software (ALAM Medical, Paris, France). Right brachial blood pressure is measured and entered into the Complior Analyse software, and then signal acquisition is launched. The operator positions the carotid sensor with the help of its specific holder and manually held the femoral sensor on the femoral artery and the distal sensor in the distal posterior tibial artery. When the operator observes 10 carotid pulse waveforms of sufficient quality, simultaneous carotid and femoral, radial and distal posterior tibial pressure curves are recorded for 10 pulse waveforms. The time delay (aortic transit time) between the two pulse waveforms is then calculated automatically. Values obtained from the carotid to femoral artery, carotid to radial artery and carotid to distal posterior tibial artery will be taken as indices of central/aortic, upper and lower limb arterial stiffness, respectively.

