### **Statistical Analysis and Data Monitorization**

Based upon a medium effect size of 0.154 derived from published changes in aortic PWV within-between modes of exercise [18], an a priori power analysis suggested that 22 participants are required to detect significant differences within-between groups, conditions and time points ( $1-\beta = 80\%$ ,  $\alpha = 0.05$ ). All data will be collated and/or analyzed using Microsoft Excel (v15.29.1, Microsoft Corporation, Redmond, Washington, United States) and Statistical Package for the Social Sciences version 24 (IBM, Armonk, New York, United States) software with results presented as mean  $\pm$  SD. Due to technical issues, missing data (~4–5%) may be evident during the study and subsequently should be replaced by averaging values before and after the missing value for the relevant variable prior to analysis.

Comparisons between interventions (Bike, Pump Power, Global Training and Control) over time (Rest vs. post-intervention time points) for indices of autonomic and vascular function will be examined via two-way

(intervention × time), repeated measures analysis of variance (ANOVA) and adjusted for sex and activity energy expenditure. Session differences for indices of autonomic and vascular function and energy expenditure will be analyzed using a one-way repeated measures ANOVA. Post-hoc comparisons will be conducted via Bonferroni's tests. Statistical significance will be set at  $p < 0.05$ .

The database will be stored in the GCP private server throughout the study period. The GCP lab will be responsible for management, storage and is the single user of the complete database.

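### HRV is derived from finger-pulse intervals although the same device takes an ECG, so transit-time changes that the sessions may themselves cause can enter the recovery HRV

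*Protocol*

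**What the plan says.** The Heart rate variability section fixes the source signal: "R-R intervals are derived from beat-to-beat blood pressure pulse intervals using finger plethysmography", in all measurement rounds. It supports the choice with one sentence, "Finger plethysmography-derived peak-to-peak intervals are highly correlated with ECG R-R intervals, with similar variability", which carries no reference and does not say whether it applies after exercise. On timing it adds that "The upstroke is determined using the pressure signal with a resolution of 2 ms". It treats HF power as the marker of parasympathetic modulation and commits acquisition and processing to the Task Force standards.

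The Advanced Hemodynamics section, describing the same device, says: "Heart rate signal (HR) will be computed from a I lead digitized electrocardiogram (ECG), included in the equipment". On layout it says: "Plethysmography sensors will be placed in the second and third finger of the right hand", with the oscillometric cuff on the same arm. The Aortic and Limb Arterial Stiffness section adds: "Right brachial blood pressure is measured and entered into the Complior Analyse software".

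The Purpose section names two targets: the time-course of parasympathetic reactivation, and changes in arterial stiffness. The Design section places the recovery rounds at 10, 20 and 30 min.

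**The concern.** The ECG gives the R-R interval directly; the finger pulse gives it with an added term. That term is the change, from one beat to the next, in the time the pressure wave takes to reach the finger. This time depends on arterial stiffness and pressure. Stiffness is the trial's other main target, and the sessions were chosen because they may change it by different amounts. The error in the autonomic outcome is thus linked to the exposure being compared and cannot be assumed equal across Bike, Pump Power, Global Training and Control, or across 10, 20 and 30 min.

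The rounds of most interest are also the most exposed. If vagal power is low soon after exercise, a transit-time variation of given size is a larger share of what is measured. A between-class difference in HF power at 10 min could then partly reflect conduit-artery behaviour and not cardiac vagal activity.

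**Working it through.** **What the documents supply.** They give the source signal, the presence of an ECG on the device, the 2 ms resolution and the recovery time points. They give no HRV mean or SD, no transit-time variability, no breathing or heart rate in recovery, and no pulse-ECG agreement data. The protocol states no figure for this error, so there is none to reproduce. Everything below other than the 2 ms is an assumption shown as a range.

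**Step 1, resolution alone.** With timing to 2 ms, each upstroke has rounding variance 2²/12 = 0.33 ms², and an interval, being a difference of two, has 0.67 ms². If half falls in the HF band (0.33 ms²), that is 0.3% of an HF power of 100 ms² and 1.7% of 20 ms². Resolution is not the problem.

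**Step 2, transit time.** Pulse interval = R-R + (transit time of next beat − transit time of this beat). At breathing frequency *f* and heart rate *h* in beats per second, this first difference has amplitude gain g = 2 sin(π*f*/*h*).

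- Recovery, assuming *f* = 0.30 Hz and 100 beats/min (*h* = 1.667): g = 2 sin(0.5655) = 1.072, g² = 1.149.
- Rest, assuming *f* = 0.25 Hz and 60 beats/min (*h* = 1): g = 2 sin(0.7854) = 1.414, g² = 2.

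Let s be the transit-time SD at the breathing frequency, r the R-R SD in the HF band, and a = g·s/r. If the two vary independently, HF variance changes by a². If they are fully coherent, it changes by between (1 − a)² − 1 and (1 + a)² − 1, depending on phase.

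| Setting | s (ms) | r (ms) | a | Independent | Fully coherent |
|---|---|---|---|---|---|
| Rest | 2 | 30 | 0.094 | +0.9% | -18% to +20% |
| Rest | 4 | 30 | 0.189 | +3.6% | -34% to +41% |
| Recovery | 2 | 8 | 0.268 | +7% | -46% to +61% |
| Recovery | 2 | 6 | 0.357 | +13% | -59% to +84% |
| Recovery | 4 | 8 | 0.536 | +29% | -78% to +136% |
| Recovery | 4 | 6 | 0.714 | +51% | -92% to +194% |

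**Step 3, a second error model.** Take instead random beat-to-beat transit jitter of SD 1-5 ms. It adds 2 × SD² to the 0.67 ms², which gives 2.67 to 50.67 ms². With half in the HF band, that is 1-25% of an HF power of 100 ms² and 7-127% of 20 ms². The pattern is the same: small when HF power is high, potentially large when it is low.

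**Step 4, cuff layout.** The finger sensors and the device's cuff are on the right arm, and a right brachial reading is taken for the pulse wave velocity acquisition. At rest, the Design section places the tonometry after the continuous recording, so those readings need not interrupt it. For recovery the order within a round is not stated. Overlap there is possible but not shown.

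**The case against.** The strongest defence is that the protocol addresses the substitution, asserting high correlation and similar variability, and follows recognised HRV standards. That is fair as far as it goes, and nothing in the documents shows the assertion to be false. But correlation between two interval series does not establish agreement in HF power, and the statement is neither referenced nor tied to post-exercise recovery. With the ECG on the same device, the assertion need not be relied on.

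The second defence is that every magnitude above rests on assumed inputs. This stands. It limits the claim to a possible error of unknown size.

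Three stronger readings are tempting and are not supported:

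- *Pulse intervals add false HF power and make reactivation look faster.* That requires transit time and R-R to vary independently. Both vary with breathing and may be phase-locked, and then the error can go either way.
- *Cuff inflations interrupt the recovery HRV series.* The recovery order is open, and the Brachial Blood Pressure section names no arm.
- *Skewed spectral powers enter the ANOVA untransformed and power is halved.* The statistical section names a repeated-measures ANOVA and says "with results presented as mean" with SD, but fixes no scale. A transformation may be set in an analysis plan that is not shown, so silence here is no error. The cost of a raw scale also depends on assumed skew. In simulations of one condition against control, with log-normal values and 80% power on the log scale, raw-scale power ran from 0.74 (mild skew, 22 participants) to 0.22 (strong skew, 12 participants). That is a loss of 8% to 73% of power. Halving or worse appeared only at a between-person log-SD of about 0.8 or more. Raw-scale type I error stayed at or below nominal.

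**Conclusion.** The point holds as a matter of signal choice. The protocol fixes HRV to a surrogate while the direct signal is available on the same device, and the surrogate's error is linked to the arterial properties that the sessions are meant to alter. The error may differ by class and time point and, for a given transit-time variation, weighs most when HF power is low.

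Size and sign cannot be determined from the documents. The illustrative recovery figures are 7-51% of HF variance under independence, with outer limits of -92% and +194% under full coherence. They rest on transit-time SD 2-4 ms, R-R HF SD 6-8 ms, 100 beats/min and breathing at 0.30 Hz. The wording should therefore be that recovery HRV may be distorted, not that it is. This merits a change because the remedy is nearly free and the affected measure serves the first-named element of the aim.

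**What to change.** 1. In the Heart rate variability section, derive R-R intervals from the device's ECG in all rounds. Use pulse intervals only where the ECG is unusable, and flag those records so that a sensitivity analysis can omit them.
2. Confirm that the ECG is stored beat to beat and not only used to display heart rate; the protocol does not say. If pulse intervals must be kept, show pulse-ECG agreement in HF power at rest and at 10, 20 and 30 min.
3. Reconcile the section's two definitions of the pulse interval, peak-to-peak and upstroke-to-upstroke, for any fallback records.
4. State the order of recordings within each recovery round, so that it is clear whether right-arm cuff readings fall inside the HRV window. If they can, that is a further reason to use the ECG.

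Optional, and not a correction of an error: if LF, HF and LF/HF prove right-skewed, analyse them on the log scale and report ratios with 95% confidence intervals.

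The cost is a change of input channel and a few sentences. If the ECG is stored, no new measurement is needed. The optional log scale means that results are read as ratios.

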## Baroreflex Sensitivity

We will use spectral method to compute baroreflex sensitivity as the transfer gain of the cross-spectra between pressure and interval in all measurement rounds. Their coherence is usually high in the 10 s rhythm band taken from 0.06 to 0.15 Hz and at ventilatory frequencies in the spectra between 0.15 and 0.5

Hz. Spectral estimates of the entire recording will be computed with the device software (Finapres® Nova, Ohmeda, Louisville, Colorado, USA), providing an easy-to-use interface [50]. A discrete Fourier transform will be used that needs no interpolation or zero padding. Triangular spectral smoothing will be set at a width of 10 for this study, in view of the 10 min duration of the records. Spectral density, coherence, pressure–interval transfer gain and phase plots are shown on the device screen and in addition a cursor allows manual selection of bands in which coherence and spectral power are high. An output program lists the resultant data and all the choices made for later analysis.

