**FIGURE 1: TIMELINE AND MAIN OUTCOME VARIABLES OF PUMPING ARTERIES**

\* INTERVENTIONS WILL BE RANDOMIZED. THE TIMELINE HEREIN DISPLAYED IS MERELY A GRAPHIC REPRESENTATION OF A PARTICIPANT'S ACTIVITIES FOLLOWING RANDOMIZATION.

In each session, participants will initially undertake 20-min of supine rest on a cushioned examination table with resting energy expenditure measured by indirect calorimetry (K5, Cosmed, Rome, Italy) and heart rate and blood pressure recorded continuously using digital plethysmography technique (Finapres® Nova, Ohmeda, 2 Louisville, Colorado, USA), followed by regional assessments of PWV and pulse wave analysis of the aortic, brachial and femoral arteries on the right side of the body using applanation tonometry (Colson Analyze, ALAM Medical, Paris, France), and carotid arterial stiffness indices and wave intensity analysis using an ultrasound (Arietta V60, Hitachi Aloka Medical Ltd, Mitaka-shi, Tokyo, Japan). In the time following, participants will perform one of three exercise sessions (Bike, Pump Power or Global Training). Exercise sessions will consist of either a 45-minute class of Bike, Pump Power, and Global Training, while energy expenditure will be continuously measured by indirect calorimetry (K5, Cosmed, Rome, Italy) (Figure 2). These sessions are characterized by distinct metabolic demands, representing the typical sessions provided by gyms and health clubs to improve or maintain cardiovascular health. In the control condition, the participants will remain quietly seated for 45-min, maintaining a good posture. Only one participant will be tested per class with approximately 10-20 non-research participants also performing each group fitness class alongside the research participants. Upon completion of each intervention/session, participants will return immediately to the examination table and recover in the supine position for 30-min while hemodynamic and stiffness indices are reevaluated at 10, 20- and 30-min following recovery and compared to those at rest.

|                       | Rest |    | Exercise Session | Recovery |    |    |
|-----------------------|------|----|------------------|----------|----|----|
|                       | 15   | 20 | 45               | 10       | 20 | 30 |
| Advanced Hemodynamics |      |    |                  |          |    |    |
| Arterial Stiffness    |      |    |                  |          |    |    |

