Next, a pulse wave Doppler ultrasound beam will be aligned to the vessel walls at the site of acquisition of the diameter waveform, to simultaneously acquire velocity data from a color flow Doppler box covering the entire vessel lumen at an angle of insonation between 60 and 65 degrees, with a sampling rate of at least 50 Hz. Spatially-averaged flow velocity will be calculated from the mean of the color Doppler data [54]. Arterial diameter and velocity will be recorded continuously for 20 s. After completing the acquisition, all data is displayed and any individual beats with noisy or unrepresentative waveforms will be rejected; all other beats (typically about 20) will be selected and signal-averaged to give single waveforms of diameter and velocity [55]. Averaged vectors for pressure and velocity, together with the electrocardiogram, and calculated net WI will be automatically displayed by the software.

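### Baroreflex sensitivity is to be read from bands picked by cursor where coherence and power look high, which can bias the gain upward and understate a post-exercise fall

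*Protocol*

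**What the plan says.** The Baroreflex Sensitivity section plans a spectral method that takes "baroreflex sensitivity as the transfer gain of the cross-spectra between pressure and interval in all measurement rounds". On frequency it first makes a general remark: "Their coherence is usually high in the 10 s rhythm band taken from 0.06 to 0.15 Hz", and likewise at ventilatory frequencies between 0.15 and 0.5 Hz. Neither range is named as the band to be analysed. The section then fixes the smoothing: "Triangular spectral smoothing will be set at a width of 10 for this study, in view of the 10 min duration of the records". After describing the plots on the device screen, it says that "a cursor allows manual selection of bands in which coherence and spectral power are high", and ends: "An output program lists the resultant data and all the choices made for later analysis".

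It gives no requirement that the band be the same in every record of a participant.

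The contrast of interest is set in the description of the sessions under Figure 1: "hemodynamic and stiffness indices are reevaluated at 10, 20- and 30-min following recovery and compared to those at rest". The statistical section carries this into an intervention × time repeated-measures ANOVA for the autonomic indices.

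**The concern.** The procedure described depends on the data. The operator looks at the coherence and power of a record and then places the band. The band can therefore differ between rest and recovery, and between classes, in the same person.

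A constant upward bias would largely cancel in a within-person comparison. This bias is not constant, because it grows as coherence falls. If coherence differs between rest and recovery, or between classes, part of that difference enters the intervention × time contrast as if it were a change in the baroreflex. The direction is unhelpful: lower coherence in recovery pushes the recovery value up and shrinks a true fall.

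Baroreflex sensitivity is one of several autonomic indices, so what is at stake is that index and not the trial as a whole.

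**Working it through.** The protocol states no figure for this point (no coherence value, no expected change in baroreflex sensitivity), so there is nothing to reproduce. The check is algebra followed by simulation.

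**Why selection biases the gain.** Write Pxx and Pyy for the smoothed pressure and interval spectra and Pxy for the cross-spectrum.

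- Gain: G = |Pxy| / Pxx
- Coherence: C = |Pxy|² / (Pxx · Pyy)
- Hence G² = C · Pyy / Pxx

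A chance excess in |Pxy| raises both G and C, so choosing high C tends to choose high G. Choosing high pressure power works partly the other way, because it avoids bins where G is inflated by a small Pxx.

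**Inputs from the protocol.** A 10-minute record, hence a frequency step of 1/600 Hz; triangular smoothing of width 10; the range 0.06–0.15 Hz. (The Advanced Hemodynamics section says "Individuals will be studied for 15 minutes". The check uses the 10 minutes on which the smoothing width is justified.)

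**Assumptions.** True gain 10; true coherence at several levels; a chosen stretch 0.03 Hz wide; width 10 read as a 10-bin window; 3,000 simulated records per level. The pressure spectrum is either flat or has a peak near 0.1 Hz, whose shape is also assumed.

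**Gradient with coherence.** With coherence-only selection on a flat spectrum, the mean gain is 10.2 at coherence 0.9, 10.7 at 0.7, 11.4 at 0.5 and 12.8 at 0.3. Gain pooled over the whole fixed band stays at about 10.0–10.1.

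**Effect of an assumed coherence drop from 0.7 to 0.3.** The last column is the true fall that would read as no change, 1 − (mean at 0.7)/(mean at 0.3).

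| Spectrum | Selection on | Mean at 0.7 | Mean at 0.3 | Fall read as no change |
|---|---|---|---|---|
| Flat | coherence only | 10.69 | 12.77 | 16% |
| Flat | coherence × power | 10.28 | 11.97 | 14% |
| Flat | power only | 10.09 | 10.59 | 5% |
| Peaked | coherence only | 10.33 | 11.84 | 13% |
| Peaked | coherence × power | 10.13 | 10.94 | 7% |

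The protocol's wording names both coherence and power, so the coherence × power rows (7–14%) fit it best.

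**What happens to larger falls.** The value read is the true ratio times (mean at 0.3)/(mean at 0.7). With coherence × power selection:

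- True 20% fall: 0.8 × 10.94/10.13 = 0.86 (peaked) and 0.8 × 11.97/10.28 = 0.93 (flat), so it reads as a fall of 14% or 7%.
- True 50% fall: 0.5 × 10.94/10.13 = 0.54 and 0.5 × 11.97/10.28 = 0.58, so it reads as a fall of 46% or 42%.

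**Noise.** At coherence 0.5 the SD of the fixed-band estimate is 0.97. It is 1.14 with coherence × power selection on the peaked spectrum (1.14/0.97 = 1.18) and 1.36 with coherence-only selection on the flat one (1.36/0.97 = 1.40). Across runs the increase is about 20–45%.

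**How much is due to averaging bins.** Averaging the bin-by-bin gain over the whole fixed band, with no selection at all, still overstates the gain at coherence 0.3 by about 8–11% with a 10-bin window. The figure is nearer 4% on a flat spectrum if width 10 means half-width, and one run with a peaked spectrum gave 15%. Summing the cross-spectrum and the pressure spectrum over the band before dividing leaves about 1–2%.

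**The case against.** The strongest objection is that the cursor sentence describes what the software can do and is not a study rule. The planned steps in that section are written with *will*, whereas the cursor merely *allows* selection. A cursor set once on 0.06–0.15 Hz would fit the text. Exact bands and reader masking are also often left to a statistical analysis plan, which is not at hand.

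Part of this stands. A reader might infer that the band is chosen afresh for every record, or that the operator knows the class and time point. The protocol states neither. The first is inferred from selection on displayed spectra and the listing of choices; the second only from the fact that the blinding described covers participants alone. Both are possibilities, not facts.

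What does not stand is that this is mere silence. The two ranges appear only as places where coherence is usually high, and the one band-reading procedure described is selection after looking at the spectra. Listing the choices makes them traceable but does not remove the bias.

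It is also fair to object that coherence-only selection on a flat spectrum ignores the power half of the stated rule, that some of the excess comes from averaging bins and not from selection, and that without a change in coherence the bias largely cancels. All three are right, and they reduce the size of the point.

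Finally, a reader might extend the point to the carotid wave-intensity recordings, where "any individual beats with noisy or unrepresentative waveforms will be rejected". That is a different device, outcome and mechanism. Nothing here shows a bias from it, and it is not part of this point.

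**Conclusion.** The point holds as a possible bias in one autonomic outcome. Reading the gain from bands picked where coherence and power look high biases it upward, more so at low coherence, and adds noise. If coherence fell from 0.7 at rest to 0.3 in recovery, a true fall of about 7–14% would read as no change under selection on both criteria; 16% is the worst case.

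It is tempting to conclude that the method would hide the post-exercise fall. The protocol does not support that. It gives no coherence values, the drop is an assumption, and a fall well above these sizes would still be seen, though understated. The figures also depend on the assumed stretch width, spectrum shape and reading of the smoothing width. The direction of the bias and its growth at low coherence were the same under both spectrum shapes and both readings of the smoothing width. The change is worth making because it is cheap and the quantity it protects is the contrast being tested.

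**What to change.** In the Baroreflex Sensitivity section:

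1. Replace manual selection with one pre-fixed band, 0.06–0.15 Hz, applied identically to every record at rest and in recovery. If the 0.15–0.5 Hz range is also wanted, report it separately with its own fixed limits.
2. Define the gain as the summed cross-spectrum divided by the summed pressure spectrum over that band. Fixing the band alone is not enough, because averaging bin gains keeps much of the low-coherence bias.
3. Report the band-average coherence beside each value, so that imprecise records can be recognised.
4. If any cursor step is kept, have the existing reader do it on files coded to hide class and time point.

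The cost is a few sentences of protocol text and, only if the cursor stays, file coding. No measurement or staff is added. The small downside is that low-coherence records give less precise values, which the reported coherence makes visible.
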